#### Statistical Analysis

Data will be analyzed and reported using the Consolidated Standard of Reporting Trials and the International Conference on Harmonisation E9 guidelines. All primary analyses will be on an intention-to-treat basis including all randomized participants.

Baseline characteristics, collected at the time of enrollment, will be cross-tabulated, according to the randomized group to check for appropriate balance and provide an overview of the study population. Baseline characteristics will be summarized as mean and standard deviation for continuous variables and as frequencies and percentages for categorical ones.

The primary outcome (proportion of thromboembolic and hemorrhagic events at a 90-d follow-up after hospital discharge) will be analyzed through an univariate logistic regression analysis to check for variables differing between groups. Variables significant at
*p*
≤ 0.10 will be included as covariates in the multilevel logistic regression model that takes into account the clustered nature of the data. As RICO is a randomized trial, we do not have a priori potential confounders. A propensity score analysis as an additional sensitivity analysis will be also performed. Considering the potential risk of an unbalanced recruitment across participating centers, the use of a multilevel logistic regression model is solid in case of unequal cluster size.
27
Secondary outcomes will be compared between groups and follow the approach detailed above for primary outcome.

Numbers and percentages of adverse events (AEs) and serious AEs will be cross-tabulated with allocated group. According to the study protocol and the primary outcome of the study, thromboembolic and hemorrhagic events will not be considered AEs.

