### Statistical Considerations

#### Sample size

In order to demonstrate a 50% reduction in the proportion of the primary outcome in the experimental group and assuming an incidence of the primary outcome of 3.5% in the control group at 90 days, 16 clusters of at least 90 patients for each group are needed to have a fixed number of equal-sized randomized clusters, with 80% power at a 5% significance level (two-sided) and with an intracluster correlation coefficient of 0.001. Considering a potential dropout rate of 5%, at least 32 centers for a total of 2,844 patients are required for the study.

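### The primary model's covariates are left to a univariate p ≤ 0.10 screen with an ambiguous target and no stated allowance for centre, so the model cannot be determined in advance

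*Protocol article*

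**What the plan says.** In the protocol article, Statistical Analysis, the primary outcome "will be analyzed through an univariate logistic regression analysis to check for variables differing between groups". Variables reaching p "≤ 0.10 will be included as covariates in the multilevel logistic regression model that takes into account the clustered nature of the data". The reason given for naming no covariates is: "As RICO is a randomized trial, we do not have a priori potential confounders". A propensity-score analysis is added as a sensitivity analysis, and secondary outcomes are to follow the same approach.

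The section gives no candidate list and no cap, and does not name a model with arm alone as primary. Clustering is mentioned only for the second step, the multilevel model.

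**The concern.** Three features of the rule cause difficulty.

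- **The adjustment set is unknown until the data are seen.** The primary odds ratio is conditional on whichever variables pass, so what is estimated can change with the sample. The same holds for every secondary outcome.
- **The target of the screen is unclear.** The grammatical subject of the sentence is the primary outcome, which suggests screening against outcome. The stated purpose is to find variables that differ between groups, which suggests screening against arm. The two give different models.
- **The screen appears to ignore centre.** Centres are the randomised units, and case mix can vary between them. If the screen compares arms as though patients had been randomised individually, its p-values are too small. It would also select on imbalance alone, so a strong predictor that happens to be balanced is left out while a weak, imbalanced variable goes in.

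At stake are the prespecification of the trial's main result and, with few events, the size of the model.

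**Working it through.** **Inputs from the protocol article, Sample size:** "assuming an incidence of the primary outcome of 3.5% in the control group at 90 days"; "In order to demonstrate a 50% reduction in the proportion of the primary outcome in the experimental group", hence 1.75% in the experimental arm; "16 clusters of at least 90 patients for each group are needed"; "with an intracluster correlation coefficient of 0.001"; 80% power, two-sided 5%; 5% dropout; total 2,844, or 1,422 per arm at 1:1 and 2,844/32 = 88.9 per centre.

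**Assumptions, not in the article:** covariate intracluster correlation (ICC) 0 to 0.10, since the stated 0.001 belongs to the outcome; 20 candidate variables, with 15 to 30 as a range. Observation and Measurements names about 14 items plus separate comorbidities.

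**1. The plan's own figure.** With 90 per centre the design effect is 1 + 89 × 0.001 = 1.089, and the effective size per arm is 1,440/1.089 = 1,322. Power for 3.5% against 1.75% is 80.4%, so the cluster design reproduces. The total of 2,844 fits only a calculation before the dropout allowance. That is a separate matter and only moves the event count between the two values below.

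**2. Expected events.** 1,422 × 0.035 + 1,422 × 0.0175 = 49.8 + 24.9 = 74.7. After 5% dropout: 74.7 × 0.95 = 70.9.

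**3. Screening against arm, centre ignored.** For a covariate with no true imbalance, the chance of passing is 2 × [1 − Φ(1.645/√DE)], with DE = 1 + 87.9 × ICC. Events per parameter are events/(number selected + 1), the 1 being arm.

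| Covariate ICC (assumed) | DE | Pass rate | Mean selected of 20 | Events per parameter (71 to 75 events) |
|---|---|---|---|---|
| 0 | 1.00 | 10% | 2.0 | 24 to 25 |
| 0.001 | 1.09 | 11% | 2.3 | 22 to 23 |
| 0.01 | 1.88 | 23% | 4.6 | 12.7 to 13.4 |
| 0.05 | 5.39 | 48% | 9.6 | 6.7 to 7.1 |
| 0.10 | 9.79 | 60% | 12.0 | 5.5 to 5.8 |

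Simulation gave 2.0, 4.6, 9.3 and 11.9 selected at ICC 0, 0.01, 0.05 and 0.10. Seven selected variables bring the ratio below 10 (71/8 = 8.9; 75/8 = 9.4). Seven or more were selected in 0.5%, 18%, 93% and 97.5% of simulated trials at those ICCs. With 15 to 30 candidates the mean number selected is 3.5 to 6.9 at ICC 0.01 and 7.2 to 14.4 at ICC 0.05.

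**4. Screening against outcome.** With 20 candidates, 5 of them assumed prognostic, about 6 are selected on average (5th to 95th percentile 4 to 9). Six give 71/7 = 10.1 to 75/7 = 10.7 events per parameter; nine give 7.1 to 7.5.

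**5. Effect on the test.** Null simulations (600 trials per setting, 20 candidates, cluster-robust logistic regression standing in for the multilevel model) rejected as follows:

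| Covariate ICC | No screening | Screened on arm | Screened on outcome |
|---|---|---|---|
| 0.01 | 7.0% | 6.8% | 6.8% |
| 0.05 | 4.8% | 4.3% | 4.0% |

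At ICC 0.05 the standard deviation of the estimated log odds ratio was 0.261, 0.261 and 0.264 respectively. A second simulation, using ordinary logistic fits, gave power of 0.822 with screening on arm and 0.835 with a prespecified risk score. The gap of 0.013 is smaller than the Monte Carlo standard error of one such figure, √(0.82 × 0.18/600) = 0.016.

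**6. The justification against the design.** Study Procedures has centres randomised first and eligible patients then evaluated within them. Informed Consent requires each patient's consent before entry. Randomising centres does not by itself rule out case-mix differences that arise when patients are enrolled after their centre's arm is fixed. The planned propensity-score analysis itself allows for such differences.

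**The case against.** The strongest defence is that no harm from the rule has been shown. In the simulations, screening did not raise type I error, and the spread of the estimate barely moved. A reader might infer from the events-per-parameter figures that the primary test is invalid or underpowered. The article and these calculations do not support that: the power difference is within simulation error, and neither simulation fitted the planned multilevel model. This objection stands and sets the severity.

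The pass rates of 23% to 60% depend on assumed covariate ICCs. They also apply only if screening is against arm and ignores centre. The second condition is inferred from the plain description of a univariate logistic regression. If screening is against outcome, those rates do not apply, and neither does the charge of ignoring prognostic strength. This also stands, which is why both readings are shown.

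The unseen analysis plan may hold a candidate list or a cap. That could limit the model's size, but the p ≤ 0.10 rule is stated here and would still choose the covariates from the data.

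If recruitment did differ by arm, adjusting for observed imbalance would be reasonable, and the propensity-score analysis addresses measured imbalance. That is a fair argument for a sensitivity analysis, but it does not fix the primary model. Nor may a reader conclude from the order of randomisation and consent that recruitment was in fact biased: the article shows only that the design permits it.

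**Conclusion.** The concern holds as a fault of prespecification. The rule as written leaves the primary model, and the models for secondary outcomes, to the data, and it can be read in two ways that give different models.

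The size is conditional. If screening is against arm with centre ignored, a nominal 10% screen passes 11% to 60% of variables with no true imbalance over assumed ICCs of 0.001 to 0.10. With 20 candidates, the model would on average be below 10 events per parameter at ICC 0.05 and above, but not at 0.01 or below. If screening is against outcome, about 6 variables enter and the ratio is near 10. Over-parameterisation is therefore possible, not certain.

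The stated reason for having no prespecified covariates does not fit a trial that randomises centres before patients are enrolled. This should be fixed; nothing here shows the planned test to be invalid.

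**What to change.** Delete the univariate screen and the p ≤ 0.10 rule. State one primary multilevel logistic model with arm, a centre random intercept, and either no covariates or a short fixed list. Draw any list from pre-intervention items that Observation and Measurements collects in both arms, for example age, prior VTE, recent bleeding and reduced mobility, taken as at admission. Four terms plus arm give 71/5 = 14.2 to 75/5 = 15.0 events per parameter.

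Do not adjust for the recorded Padua or IMPROVE Bleeding Scores, which are collected in the experimental group only. Do not adjust for antithrombotic therapy during the stay, which the intervention is meant to influence. Report the other model (arm-only or adjusted) and the planned propensity-score analysis as sensitivity analyses, and apply the same structure to secondary outcomes. Replace the sentence on confounders.

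The cost is a change of wording before database lock; a list confined to these items needs no new data. The downside is that imbalances outside the list are handled only in sensitivity analyses.

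### The 80% power holds only for equal-sized centres with all 2,844 patients evaluable; the multilevel model offered against unbalanced recruitment protects validity, not power

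*Protocol article*

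**What the plan says.** The Sample size section of the protocol article fixes these design inputs:

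- Event rate: "assuming an incidence of the primary outcome of 3.5% in the control group at 90 days".
- Effect: "In order to demonstrate a 50% reduction in the proportion of the primary outcome in the experimental group", that is, 3.5% against 1.75%.
- Error rates: 80% power, two-sided 5% level.
- Clusters: "16 clusters of at least 90 patients for each group are needed", described as "a fixed number of equal-sized randomized clusters".
- Clustering: "with an intracluster correlation coefficient of 0.001".
- Total: 32 centres and 2,844 patients as a minimum, stated after mention of a possible 5% dropout.

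The Statistical Analysis section raises the possibility that centres will recruit unevenly. Its answer is that "the use of a multilevel logistic regression model is solid in case of unequal cluster size". Neither section gives a CV of cluster size or a design effect for unequal clusters. Dropout is the only allowance mentioned.

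**The concern.** The two sections do not fit together. One computes power on the assumption that centres are the same size. The other says this assumption may fail and offers a remedy for a different problem.

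A random-intercept logistic model gives valid estimates and standard errors when cluster sizes differ. It cannot undo the fact that, for a fixed total, patients concentrated in a few large centres carry less independent information than the same number spread evenly. A reader who takes the two sections together may believe that 80% still applies under uneven recruitment. What is at stake is the accuracy of the power figure, not the validity of the primary analysis.

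**Working it through.** **Inputs.** From Sample size: p1 = 0.035, p2 = 0.0175, two-sided alpha 0.05, ICC 0.001, 32 centres, 2,844 patients, 5% dropout. Assumed: CV of cluster size 0.5, 0.7 or 1.0, because the article gives none.

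**Step 1: reproduce the plan's figure.** Without clustering, with unpooled variance:

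n per arm = (1.960 + 0.842)² × (0.035×0.965 + 0.0175×0.9825) / 0.0175² = about 1,306 (1,310 with pooled variance).

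The mean size is m = 2,844/32 = 88.9. For equal clusters the design effect is DE = 1 + (m − 1)×ICC = 1 + 87.9×0.001 = 1.088. Then 1,306.3 × 1.0879 = 1,421.1, rounded up to 1,422 per arm, or 2,844 in all. The stated total therefore coincides with the requirement for equal clusters and complete data. At 16 × 90 per arm, DE is 1.089 and power is 80.4% (pooled), so the stated 80% reproduces.

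**Step 2: unequal sizes.** DE = 1 + ((1 + CV²)m − 1)×ICC. At CV 0.7, for example, DE = 1 + (1.49×88.9 − 1)×0.001 = 1.131. The effective number per arm is 1,422/1.131 = about 1,257, and power = Φ(0.0175×√1,257/√0.05097 − 1.960) = 78.5%.

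Each power cell shows unpooled / pooled variance:

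| CV (assumed) | DE, 2,844 evaluable | Power, 2,844 | DE, about 2,702 evaluable | Power, about 2,702 |
|---|---|---|---|---|
| 0 | 1.088 | 80.0 / 79.9% | 1.083 | 78.1 / 78.1% |
| 0.5 | 1.110 | 79.2 / 79.1% | 1.105 | 77.4 / 77.3% |
| 0.7 | 1.131 | 78.5 / 78.4% | 1.125 | 76.6 / 76.5% |
| 1.0 | 1.177 | 76.9 / 76.8% | 1.168 | 75.1 / 75.0% |

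The right-hand columns take the 5% dropout out of the stated total: 2,844 × 0.95 = 2,701.8, so m = 84.4.

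**Step 3: does the multilevel model recover the loss?** The design effect in step 2 describes an analysis that weights centres by size. For a multilevel analysis with near-optimal weights, the efficiency relative to equal clusters is 1 − CV²×L×(1 − L), with L = m×ICC/(m×ICC + 1 − ICC). Here L = 0.0889/(0.0889 + 0.999) = 0.082, so at CV 1.0 the efficiency is 1 − 0.082×0.918 = 0.925. Power (unpooled) is then 79.3%, 78.5% and 76.9% at CV 0.5, 0.7 and 1.0, within 0.1 point of the table. A simulation that fitted the random-intercept logistic model to 3,000 trials with gamma-distributed centre sizes gave 80.1% with equal sizes and 77.3% at CV 0.7 (Monte Carlo standard error about 0.75 point). At this ICC the model recovers essentially nothing.

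**The case against.** **The quoted sentence is true.** It stands in the analysis section, concerns the model and does not mention power. A reader might infer that the plan claims the model preserves power, or that it expects imbalance. Neither is in the text, which makes no power claim for the model and speaks only of a potential risk. This objection stands. The point is that the power figure and the named risk are never brought together.

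**The loss is small.** At the stated ICC it is about 0.8 point at CV 0.5, about 1.5 at CV 0.7 and about 3 at CV 1.0, and every CV is an assumption. This stands and sets the weight of the point.

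**A larger ICC would look worse.** At an assumed ICC of 0.005, power would be about 68% with equal clusters and about 62% at CV 0.7. A reader might take this as evidence of a serious loss from unequal sizes. It is not: 12 of those 18 points come from the ICC, and the article does not state that ICC. At that value a multilevel analysis also does slightly better than the size-weighted formula, about 63.5% at CV 0.7.

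**The floor of 90 per centre protects power.** If every centre reached 90, extra patients in larger centres could only add information, and power would not fall below about 80.4%. But 32 × 90 = 2,880 exceeds 2,844, so the floor cannot hold in every centre within the stated total.

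**An article condenses, and the full protocol may hold a CV allowance.** That would answer a mere omission. Here the article itself states equal sizes, and step 1 shows that 2,844 leaves no room for a hidden allowance.

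**Conclusion.** The point holds as a minor one. The stated 80% is the power for equal-sized centres with all 2,844 patients evaluable, and the model choice does not extend it to uneven recruitment. For CV 0.5 to 1.0 at ICC 0.001, power is about 77 to 79% if all 2,844 are evaluable, and about 75 to 77% if the 5% dropout comes out of that total.

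On the second reading, 2 of the points below 80% come from dropout rather than cluster size. How 2,844 relates to dropout is a separate question, and it matters here only because it leaves no reserve.

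The figures rest on the plan's event rates and ICC, on an assumed CV, and on a normal approximation. A t reference with 30 degrees of freedom would lower them all: at 2,844, to 77.4% with equal sizes and 74.1% at CV 1.0. Nothing here shows that the trial is badly underpowered or that its primary analysis is invalid.

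**What to change.** In Sample size, state an assumed CV of cluster size and restate power with DE = 1 + ((1 + CV²)m − 1)×ICC, applied to the number evaluable after dropout. On the plan's own inputs this gives about 75 to 77% for CV 0.5 to 1.0. The range of 77 to 79% is right only if 2,844 patients are evaluable.

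In Statistical Analysis, add to the sentence on the multilevel model that it handles unequal sizes for validity and not for power.

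The cost is two sentences and a slightly less favourable power figure. Endpoint, model and patient procedures stay as they are. The working here supports no particular ceiling on recruitment per centre.

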**Methods**
 Reducing Important Clinical Outcomes in hospitalized medical ill patients (RICO) is a multicenter, cluster-randomized, controlled clinical trial (ClinicalTrials.gov Identifier: NCT04267718). Acutely ill patients hospitalized in Internal Medicine wards are randomized to the use of RAMs—namely the Padua Prediction Score and the International Medical Prevention Registry on Venous Thromboembolism Bleeding Score—or to clinical judgement. The primary study outcome is a composite of symptomatic objectively confirmed VTE and major bleeding at 90-day follow-up. Secondary endpoints include the evaluation of clinical outcomes at hospital discharge and the assessment of VTE prophylaxis prescription during the study period. In order to demonstrate a 50% reduction in the primary outcome in the experimental group and assuming an incidence of the primary outcome of 3.5% in the control group at 90-day; 2,844 patients across 32 centers will be included in the study.

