### Study Endpoints

The primary endpoint of the study is to assess the efficacy of a systematic evaluation of the thromboembolic and bleeding risk in reducing the composite rate of thromboembolic and hemorrhagic events in hospitalized, acutely ill medical patients at a 90-day follow-up.

Secondary endpoints include (i) the evaluation of clinical outcomes (VTE, major bleeding, cardiovascular events) at the time of hospital discharge (i.e., discharge at home, transfer to another unit, or death) and (ii) the assessment of VTE prophylaxis prescription during hospital stay and at the time of discharge.

As thromboprophylaxis has been shown to have the potential to reduce arterial events as well,
22
23
24
25
information about arterial events (e.g., stroke, acute myocardial infarction, peripheral artery disease) has been collected and will be analyzed as an exploratory outcome.

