#### Observation and Measurements

For each enrolled patient, the following information during the hospital stay is collected: age, sex, height, and body weight (to compute body mass index), comorbidities, past medical history (with special consideration for history of VTE and recent [i.e., <3 months] history of bleeding), functional status (chronically bedridden, reduced mobility, support of a caregiver), antithrombotic and/or hormonal therapies, laboratory tests (in particular hemoglobin, platelet count, creatinine clearance), occurrence of objectively confirmed venous thromboembolic events and/or major bleeding events (according to International Society on Thrombosis and Haemostasis criteria), any other clinically relevant events, Padua Prediction Score and IMPROVE Bleeding Score (for the experimental group only), and outcome of hospitalization (discharge, transfer to another unit, death).

All patients are evaluated after 90 days through a telephone call or during an outpatient visit, if planned. The following information is collected: patient status (survival or death, in the latter case date and possible cause of death should be recorded), occurrence of objectively confirmed venous thromboembolic events and major bleeding, any other clinically relevant event, possible rehospitalization and related cause, and current antithrombotic therapies, if any. Clinical records relevant to venous thromboembolic events and major bleedings will be made available to an independent Adjudication Committee for evaluation.

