#### Safety Procedures

All drugs used in this study are part of the standard-of-care according to the indications specified in the marketing authorization. The report of a suspected adverse reaction to these drugs in patients enrolled in the study is collected and reported based on current laws (D.M. April 30, 2015, as a transposition of European directives 2010/84/UE e 2012/26/UE) by filling a report form of suspected adverse reaction within the time specified by the law.

The report form can be filled electronically by accessing the platform Vigifarmaco (
www.vigifarmaco.it
) through the guided procedure, manually by paper or by fax or e-mail to the Local Pharmacovigilance Manager of the hospital. In addition, a copy of the form must be emailed or faxed to the study promoter.

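### The adverse-event exclusion is worded more widely than the primary outcome that justifies it; read literally, it drops non-major bleeding from the by-arm harm tables

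*Protocol article*

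**What the plan says.** The Statistical Analysis section of the protocol article plans one harm analysis outside the endpoints: "Numbers and percentages of adverse events (AEs) and serious AEs will be cross-tabulated with allocated group". The next sentence removes a class of events from it. It opens with "According to the study protocol and the primary outcome of the study" and concludes that "thromboembolic and hemorrhagic events will not be considered AEs". It sets no limit by severity, confirmation or adjudication.

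The primary outcome is defined most exactly in the Methods part of the abstract: "The primary study outcome is a composite of symptomatic objectively confirmed VTE and major bleeding at 90-day follow-up". The Observation and Measurements section collects major bleeding by ISTH criteria and adds that "Clinical records relevant to venous thromboembolic events and major bleedings will be made available to an independent Adjudication Committee for evaluation". Among the secondary endpoints, the clinical ones are "the evaluation of clinical outcomes (VTE, major bleeding, cardiovascular events) at the time of hospital discharge". Arterial events are an exploratory outcome (Study Endpoints).

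**The concern.** Keeping endpoint events out of the AE tables is a usual way to avoid counting them twice. It works when the excluded class and the endpoint are the same class. Here the excluded class is worded as all thromboembolic and all haemorrhagic events, while the endpoint takes in only part of them. Whatever lies between the two is at risk of appearing in no by-arm analysis.

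For bleeding, that gap is the non-major bleed. The trial tests a strategy for deciding on thromboprophylaxis, and one of its two scores is a bleeding score, so bleeding of any severity is a natural part of the harm comparison. The named endpoints report major bleeding as a separate item only at hospital discharge; after discharge it enters them only inside the 90-day composite. The AE and serious AE tables are the only other stated place where the arms are compared on harm.

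**Working it through.** No arithmetic applies: the point contains no figure, and the documents give no rate of non-major bleeding. The check sets the exclusion beside the endpoint definitions, under two readings of the exclusion.

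- **Literal reading:** every thromboembolic or haemorrhagic event is barred from the AE tables.
- **Endpoint reading:** only events that count toward the primary outcome are barred.

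| Event | Named endpoint | In AE tables, literal reading | In AE tables, endpoint reading |
|---|---|---|---|
| VTE, symptomatic and objectively confirmed | Primary; VTE is also secondary at discharge | No | No |
| Major bleeding (ISTH) | Primary; also secondary at discharge | No | No |
| Arterial events | Exploratory; cardiovascular events are secondary at discharge | No, where thromboembolic | Yes, if recorded as AEs |
| Non-major bleeding | None named | **No** | Yes, if recorded as AEs |

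1. The first two rows are sound under either reading. These events are compared by arm as endpoints.
2. Arterial events are compared by arm under either reading, because the Study Endpoints section assigns them to an analysis.
3. Non-major bleeding is the row that depends on the reading. Under the literal one it has no endpoint and no place in the AE or serious AE tables.
4. Such a bleed may still be recorded. Observation and Measurements has a catch-all item for other events of clinical relevance, both in hospital and at 90 days, and also asks at 90 days about rehospitalization and its cause. Under Safety Procedures, "The report of a suspected adverse reaction to these drugs in patients enrolled in the study is collected and reported based on current laws", with no exemption for bleeding.
5. These routes collect or report the event. Neither is tied to a stated comparison between arms.

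**The case against.** The strongest reply is that the phrase is simply the article's label for the composite. The Trial Design and Objectives, Study Endpoints and Discussion sections use it so, and the Statistical Analysis section itself writes "The primary outcome (proportion of thromboembolic and hemorrhagic events at a 90-d follow-up after hospital discharge". As the exclusion also opens by invoking the primary outcome, it can be read as removing endpoint events only, and the proposed limit would then do little more than spell out what was meant.

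This reply is fair and lowers the weight of the point. It does not dispose of it: it shows that the sentence can be read in two ways, not that it is right as worded. Someone building the AE tables from the sentence alone would leave out every bleed.

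A reader might infer four stronger conclusions, which the documents do not support:

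- **Non-major bleeding is counted nowhere.** It can be recorded as another clinically relevant event or reported as a suspected adverse reaction. Only the by-arm comparison is unstated.
- **Bleeds that the Adjudication Committee does not confirm are lost.** The article does not say how they are handled. A condensed article may leave that to the full protocol or analysis plan, and under the endpoint reading such events would not be barred from the AE tables.
- **The exclusion contradicts Safety Procedures.** That section covers legal reporting of suspected drug reactions; the exclusion covers statistical tabulation. An event can be subject to both.
- **Safety would look better than it is in the experimental arm.** The wording applies to both arms, and the Discussion cites a before-and-after study in which risk scores were followed by less pharmacological prophylaxis (43.3% against 56.7%). The direction of any effect on the comparison is therefore unknown.

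**Conclusion.** The concern holds in a limited form. The exclusion is wider in wording than the outcome cited as its reason. Under the literal reading, all non-major bleeding is absent from the AE and serious AE tables of both arms, with no named endpoint to take it up. Under the endpoint reading nothing is lost, but the sentence lacks the words that would say so.

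The size in events cannot be given. The conclusion rests on two assumptions: that the abstract's definition of the primary outcome is the operative one, and that the full protocol or analysis plan, which is not at hand, does not already narrow the exclusion. The point is minor. The primary outcome, its analysis and the sample size are unaffected.

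**What to change.** Reword the exclusion so that only confirmed primary-outcome events, that is VTE and major bleeding meeting the outcome definition, are left out of the AE and serious AE tables. Add that all other bleeding is tabulated by arm in those tables, using the event information already collected in hospital and at 90 days.

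The cost is one sentence and one extra table. The limitation is completeness: the listed bleeding outcome is major bleeding, and lesser bleeds reach the data only through the general item on other events or a reaction report. Minor bleeds will be captured incompletely, and a note to the table should say so.
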